***Secondary outcomes***

We will additionally look at the incremental benefit of HCVST efficacy in promoting HCV testing, number of newly identified cases of HCV, the linkage to HCV clinical care after self-testing, and HIV, chlamydia and gonorrhea testing within four weeks.

We will examine cost-effectiveness alongside the trial. Using a decision-tree model, we will calculate the cost per person tested for HCV (includes both self-testing and facility-based testing), cost per person self-tested for HCV, cost per person tested for HCV in a facility, and cost per person diagnosed with HCV. We will also examine the incremental cost-effectiveness ratio comparing the two arms of the trials. We will conduct deterministic univariate sensitivity analyses and probabilistic sensitivity analysis to examine the robustness of our findings.

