**Study setting and population**

Participants are eligible if they are born biologically male, age 18 years or above, having anal sex with other men, reporting not testing for HCV in the past year, reporting at least one of the following risk factors in the past year (condomless anal sex or STD diagnosed or injection drug use), plan to live in China for the next month and have a stable residence where they can securely receive a postal package. Participants are excluded if they are participating in similar clinical trials or other programs involving HCV testing or unwilling or unable to comply with all the requirements of the study. All enrolled participants will be divided into the two trials according to their HIV status. All participants will be recruited from seven MSM-led clinics run by MSM-focused community-based organizations(CBOs) in seven provinces located in different parts of China: East China (Shandong Province), [South China](https://en.wikipedia.org/wiki/South_Central_China) (Guangdong Province), [Northeast China](https://en.wikipedia.org/wiki/Northeast_China) (Liaoning Province), Northwest China (Qinghai Province), Central China (Hubei Province), Southwest China (Chongqing), and North China (Hebei Province). All the MSM-led clinics offer free HIV and syphilis testing and counseling for MSM. Staff at each CBO site also have rich experience in HIV/syphilis counseling and intervention. All the MSM living with HIV will be recruited offline and HIV-negative MSM will be recruited by half of the online and offline ratios through CBOs. All study sites will follow the same research procedure.

All participants will be asked to finish a baseline survey for eligibility screening through Wenjuanxing (an online survey platform belonging to Changsha Ranxing Information Technology Co., Ltd, China). Online informed consent will be obtained before the baseline survey by clicking on a “button” indicating that the participant has read the consent form and agrees to participate in this research.

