***HCVST arm***

In this arm, participants will receive SOC arm interventions. Additionally, participants in this arm will be offered HCV self-testing kits for free. Participants can order self-testing packages online and apply for free home delivery through WeChat or Wenjuanxing and are allowed a maximum of one self-testing package for the duration of the study. Each HCV self-testing package contains equipment for blood sample collection, quick HCV test and a step-by-step pictorial instruction and operation video for using the self-testing kit. The provision of HCV self-testing service will last for four weeks. In this study, we will use the ABON HCV Hepatitis C Virus Antibody Rapid test kit, which advertises a sensitivity and specificity of 99.53% and 99.78%, respectively[16].

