**Follow-up support**

An HCV counselor will be in charge of care support through WeChat or telephone (office hours: 8:00 am to 5:30 pm, Monday to Friday). Care support will include HCV pre-test counseling, instruction for the HCV self-testing kit, explanation of testing results, advice on reactive testing results and other relevant emergencies. All the inquiry logs will be kept. Participants are advised to inform the HCV counselor of any reactive self-testing results and will be referred to the designated hospital for confirmatory laboratory testing and clinical examination based on the standard protocols of the respective clinics. If participants are diagnosed with HCV, further follow-up will include HCV confirmatory testing and treatment information.

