**Outcome**

***Primary outcome***

The primary outcome is the HCV testing rate (including facility testing and self-testing) within four weeks, excluding confirmatory tests after a positive self-test. All testing results will use photo verification for validation. A participant will only be counted as having the primary outcome if the participant has submitted a photo including age, test date, and anti-HCV IgG results to research team through WeChat or the online platform.

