**Surveys**

***Baseline survey***

All participants will complete the baseline survey on the online survey platform (Wen Juan Xing, https://www.wjx.cn) at the time of registration. The baseline survey asks questions about their sociodemographic characteristics and sexual behaviors. After completing the survey, participants will receive 20 RMB (approximately 3 USD).

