***Analysis plan***

*Primary outcome*

The primary outcome of HCV testing rate (including facility testing and self-testing) within four weeks will be evaluated using a difference in proportions. We are interested in determining whether there is an overall difference in HCV testing rates between the arms. There may be differences in patient populations across provinces (NGOs), so we will adjust for NGO in the analysis if there is evidence of such differences. The appropriate approach for such an analysis will depend on the frequency of testing in each arm. A model-based approach that uses identity link and binomial family can be used to adjust for NGO if the frequencies are not too extreme (e.g., too few testers in SOC). Otherwise, a stratified test like Cochran–Mantel–Haenszel can be used to produce an adjusted *P*-value. We may also consider pooling data from NGOs that have low frequencies in the SOC arm (e.g., 0 or 1 testers) prior to adjusting for NGO.

*Secondary outcomes*

Secondary outcomes of testing rates for HIV, chlamydia, and gonorrhea will be also be evaluated as a difference in proportions using the methods described for the primary outcome.

*Economic evaluation*

We will estimate the total unit and incremental unit cost for each arm in two trials. All costs will be categorized as startup costs, fixed costs and variable costs in this study. Start-up costs refer to the cost which are incurred in the process of study beginning, including coordination of survey platforms. Fixed costs refer to the cost which cannot change with the number of participants during the whole trial period, including venue and equipment cost. Variable costs refer to the cost which are expenses that vary with the number of participants used, including HCVST kits, postage and other consumables. We will calculate all the costs for each arm, and then this cost will be divided by the number of MSM tested and the number of newly detected HCV cases in each study arm to calculate incremental unit costs. In addition, the univariate, multivariate and probabilistic sensitivity analyses from a decision tree model will be used to examine uncertainty.

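### The count of new HCV cases, and the cost per case built on it, cannot be reliably established from the data collection the protocol describes

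*Protocol*

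**What the plan says.** One quantity appears under three labels, none of them defined. Protocol, Secondary outcomes, lists "number of newly identified cases of HCV" and, among the economic outcomes, "cost per person diagnosed with HCV". The economic evaluation in the Analysis plan divides costs by "the number of newly detected HCV cases in each study arm".

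The data that would feed this count are described as follows.

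- **Eligibility** (Study setting and population): the only condition on HCV history is "reporting not testing for HCV in the past year". Known, cleared or treated HCV is not an exclusion.
- **Baseline survey**: "The baseline survey asks questions about their sociodemographic characteristics and sexual behaviors".
- **Verified result** (Primary outcome): "a photo including age, test date, and anti-HCV IgG results". The kit supplied is the "ABON HCV Hepatitis C Virus Antibody Rapid test kit" (HCVST arm). Photos are of the used kit or of the facility report (HCV testing record and results).
- **Confirmation** (Follow-up support): a participant who tells the counsellor of a reactive self-test is referred to hospital for confirmatory laboratory testing. The section then ends: "If participants are diagnosed with HCV, further follow-up will include HCV confirmatory testing and treatment information".
- **Follow-up survey**: both arms are asked about the method and results of HCV tests in the four weeks.

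**The concern.** An antibody result does not by itself show a new or current infection, and the protocol accepts this when it sends reactive self-tests for confirmation. Three gaps then matter.

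1. *New* has no described support. A man diagnosed more than a year ago can enrol, and nothing described at baseline would identify him.
2. *Diagnosed* is used inconsistently. Under Follow-up support a reactive self-test leads to confirmation, but the next sentence has men who are already diagnosed going on to confirmatory testing. This word sets the denominator of cost per case.
3. Explicit referral for confirmation follows the self-test route. The route recommended to the SOC arm is a facility test, and no matching referral is written for a reactive facility result. Cases are nevertheless counted in each arm.

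At stake are a named secondary outcome, the cost per case in both trials, and the closing claim about earlier diagnosis of HCV. A later analysis plan can define a case, but it cannot recover history or confirmatory results that were not recorded.

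**Working it through.** **No planned figure to reproduce.** The protocol gives no expected number of cases. Its sample sizes concern the testing rate. They reproduce with an arcsine approximation to Fisher's exact test (13/0.8 = 16.25, so 17 per arm; 21/0.8 = 26.25, so 27 per arm) and are not affected.

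**Inputs from the protocol**

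- Men per arm: 42 in each trial (Sample size).
- Pilot uptake, HCVST arm: 15/19 in trial 1, 2/5 = 0.40 in trial 2. SOC arm: 2/19 and 0/5 (Table S2).
- Prevalence in China: 1.2% in general MSM, 8.4% in MSM living with HIV (Background).
- Kit sensitivity 0.9953 and specificity 0.9978 (HCVST arm).

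**Assumptions.** The prevalences are read as antibody prevalence, and the general-MSM figure is applied to HIV-negative men.

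**Formulas**

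- Tested = 42 × uptake
- True reactives = tested × prevalence × 0.9953
- False reactives = tested × (1 − prevalence) × (1 − 0.9978) = tested × (1 − prevalence) × 0.0022

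**HCVST arm, trial 1**

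- Tested: 42 × 15/19 = 33.2
- True: 33.2 × 0.012 × 0.9953 = 0.40
- False: 33.2 × 0.988 × 0.0022 = 0.07
- Total about 0.47, of which 15% false

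**HCVST arm, trial 2**

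- Tested: 42 × 0.40 = 16.8
- True: 16.8 × 0.084 × 0.9953 = 1.40
- False: 16.8 × 0.916 × 0.0022 = 0.03
- Total about 1.44, of which 2.4% false

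**Range**

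- If all 42 men tested: 0.50 + 0.09 = 0.59 (trial 1) and 3.51 + 0.09 = 3.60 (trial 2).
- At pilot uptake with the global prevalences in the Background (1.5% and 6.3%): 0.50 + 0.07 = 0.57 and 1.05 + 0.03 = 1.09 (from unrounded terms).

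**SOC arm, antibody-positive men among those tested**

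- Trial 1: 42 × 2/19 × 0.012 = 0.05
- Trial 2: zero at pilot uptake; at the 10% SOC rate assumed under Sample size, 42 × 0.10 × 0.084 = 0.35

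**What cannot be computed.** The share of antibody-positive men who already knew of their infection is not in the document. The Background gives 41% lifetime HCV testing among Chinese MSM, so an earlier diagnosis is possible. But that figure includes men tested in the past year, who are ineligible, and it says nothing about how many tested positive.

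**The case against.** The strongest reply is that this is an undefined secondary outcome whose definition belongs in the analysis plan. Several parts of that reply stand.

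- **A reader might infer that past, known or falsely reactive men will be counted as new diagnoses.** No passage says an unconfirmed antibody result is a case. The photo rule defines the testing outcome, and a confirmed-case definition would be compatible with Follow-up support. The text supports *could be counted*, no more.
- **A reader might infer that confirmation happens in one arm only.** The last sentence of Follow-up support names no arm, counselling on reactive results is not limited to self-tests, and self-test costs are reimbursable for all participants. The difference is by test route, and therefore mainly by arm.
- **A reader might infer that HCV history is certainly not collected.** The description of the baseline survey is a one-sentence summary. The same survey screens eligibility, so it must hold items that the summary omits. The sound statement is that no history item is described.
- **Some confirmatory results might be captured anyway.** The follow-up survey asks both arms for test method and results, and counsellor inquiries are logged. Neither is specified as recording a confirmatory result or an earlier diagnosis.
- **The ordering of diagnosis and confirmation may be loose drafting**, with the last sentence meaning information about both confirmation and treatment. That reading is possible, but the term still drives a denominator.
- **The sensitivity of cost per case to one man is a sparse-data problem under any definition.** True. Small numbers make a clear definition more important, but they are not themselves caused by this gap.

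What the reply does not answer is that a definition written later depends on history and confirmation having been recorded.

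**Conclusion.** The concern holds in a limited form. As described, the data collection does not reliably separate new from past or already-known infection, or confirmed from unconfirmed results, in the same way in both arms. The two statements on diagnosis and confirmation under Follow-up support do not agree.

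The absolute numbers are small: about 0.5 and 1.4 reactive men expected in the HCVST arms of trials 1 and 2, and well under one positive man in either SOC arm. False reactives are a minor part (0.07 and 0.03 men). Past or known infection is the main exposure, and its size is unknown. It would be tempting to quote a factor by which cost per case is understated, but any such factor would rest wholly on assumed shares of known and confirmed men, so none is given. With so few cases, however, reclassifying one man could halve, double or remove the cost-per-case figure.

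These counts rest on pilot uptake from 38 and 10 men and on the two prevalence assumptions stated above. The primary outcome, the sample size and the cost per person tested are unaffected.

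**What to change.** 1. Use one case definition in both arms and in both the secondary outcome and the economic evaluation: no previous HCV diagnosis reported at baseline, and a positive confirmatory result whichever route gave the first reactive test.
2. Add one baseline item on previous HCV diagnosis, or state that the full questionnaire already holds one.
3. Collect confirmatory results in both arms through the existing photo upload, follow-up survey or counsellor log.
4. Report antibody-reactive men as a separate count in each arm.
5. Show cost per case twice: with unconfirmed reactive men counted as cases, then as non-cases.
6. Reconcile the two Follow-up support sentences on diagnosis and confirmatory testing. How confirmation is arranged clinically is for the investigators; the point here is what is recorded and counted.

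The cost is one survey question, one further upload or log field, and a revised outcome definition. The downside is a smaller case count, a less favourable cost per case, and some reactive men still unconfirmed at four weeks.

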**Data collection**

***HCV testing record and results***

HCV testing results can be either from self-testing or facility-based testing. HCV self-testing will be confirmed by photo verification of the used testing kit. Facility-based HCV testing and the result will be confirmed by photo verification of the test report. Participants can securely upload testing results through WeChat or Wenjuanxing Platform. A research assistant will conduct the verification process by checking the uploaded photos. Participants in all arms who upload photo verification will get 5 RMB (approximately equal to 0.8 USD dollars). All participants will be informed at enrolment that cost of HCV testing including facility-based HCV antibody testing and HCV self-testing during the four-weeks study period can be reimbursed by providing a photo of test report and receipt.

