HCVST kits have been approved for HCV screening in China, which can be accessed through e-commerce platforms (Taobao and Jingdong). However, there are limited studies to evaluate the effectiveness and cost-effectiveness of HCVST compared to traditional facility-based testing. The purpose of this protocol is to design two parallel randomized controlled trials to evaluate the effectiveness and cost of providing HCVST on increasing the frequency of HCV testing compared with standard-of-care: one in HIV-negative MSM (trial 1) and one in MSM living with HIV (trial 2) in China.

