**Methods**

**Study design**

Two parallel, unmasked, individual-level, randomized controlled trials will be conducted among MSM. All enrolled MSM will be offered to join one of the two trials according to their HIV status. In trial 1, we will enroll MSM who had a HIV-negative result according to their testing report in the past three months. In trial 2, we will enroll MSM who had a HIV-positive result determined by testing report. In each trial, all participants will be randomly assigned in a 1:1 ratio into one of two arms: standard of care (control arm) and HCVST. The SOC arm will receive a community-based message and postcard to be encouraged to take anti-HCV IgG testing at local clinics. In addition to the message and postcard for men in the SOC arm, the HCVST arm will be provided with free HCVST kits during the study period. Participants in each arm will be followed for four weeks (Fig. 1). Preliminary data from a pilot study will be used to inform the final trial design.

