Several other challenges may be encountered during the study implementation. First, participants in HCVST arm will be provided HCV self-testing kits for free, while participants in SOC arm need to pay for their HCV test, which could lead to a different level of testing incentive and reduce the comparability between the two arms. Therefore, all the participants will be informed that cost of any facility-based HCV testing during the four-week period can be reimbursed by providing their test report and receipt to the investigator. Second, HCVST may not adequately connect users with post-testing services, such as confirmatory testing and management of those who test users. In this study, all participants will be recruited through a local CBO, which could be helpful for the subsequent linkage to care. Third, the four weeks duration of follow-up will limit the ability of the study to assess the long-term effect of the intervention on HCV. Fourth, to protect the confidentiality of MSM, especially for MSM living with HIV, names and other specific identifying information will not be collected. All data will be encrypted and stored in remote repositories.

Another potential limitation of this study is the potential for sampling bias since the participants will be recruited through CBOs. Thus, this recruitment strategy will exclude participants who are less likely to visit these CBOs[21]. Besides, all the recruitment sites are in the central district of cities, which may also lead to sampling bias and restrict the generalizability of results to MSM living in non-urban settings.

In conclusion, this study will compare the effectiveness and cost-effectiveness of HCVST and traditional facility testing services among HIV-negative and MSM living with HIV. Finding from this study will help explore whether HCVST can make up for the shortcomings of traditional facility testing services by improving the early diagnosis rate of HCV.

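### The protocol gives two scopes for one enrolment reimbursement notice, and the wider one removes the price of self-testing for men in the standard-of-care arm

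*Protocol*

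**What the plan says.** **Reimbursement, Data collection (HCV testing record and results).** All participants are to be told at enrolment that the "cost of HCV testing including facility-based HCV antibody testing and HCV self-testing during the four-weeks study period can be reimbursed". On proof, the cost "can be reimbursed by providing a photo of test report and receipt". Nothing limits the self-testing part to the HCVST arm.

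**Reimbursement, Discussion.** The protocol recognises a price gap: "participants in HCVST arm will be provided HCV self-testing kits for free, while participants in SOC arm need to pay for their HCV test". Its answer is that "all the participants will be informed that cost of any facility-based HCV testing during the four-week period can be reimbursed". Self-testing is not mentioned.

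**Contrast between arms, Study design.** "In addition to the message and postcard for men in the SOC arm, the HCVST arm will be provided with free HCVST kits". The HCVST arm section and Table S1 add that the package is ordered through the study, delivered home free, limited to one per man, and comes with pictorial instructions and a video.

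**Access outside the trial, Background.** Approved kits can be bought on e-commerce platforms.

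**Primary outcome.** A verified HCV test of either kind, in either arm, within four weeks.

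**The concern.** Sites have to give one message at enrolment, and the protocol describes that message in two ways. The difference falls almost entirely on the control arm: a man in the HCVST arm has little or no self-test cost to reclaim, whereas a SOC man who buys a kit online does.

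If the wider notice is given, every control is told that self-testing exists as an option and that its cost can be recovered. The free kit is the one component meant to separate the arms, and the Discussion presents the study as a comparison of HCVST with traditional facility testing. Self-tests bought by SOC men would enter the primary outcome as SOC successes and shrink the estimated difference. They would also enter the SOC cost per person tested and the incremental cost-effectiveness ratio, so the comparator would no longer be purely facility-based. Information given at enrolment cannot be undone in the analysis.

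**Working it through.** **Step 1. The two accounts side by side**

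| | Data collection | Discussion |
|---|---|---|
| Who is told | All participants | All participants |
| Period | Four weeks | Four weeks |
| Tests named | Facility-based and self-testing | Facility-based |
| Reason given | None | Price gap between arms |
| Proof | Photo of report, and receipt | Report and receipt |

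Audience and period agree; only the scope differs. The reason given in the Discussion, that SOC men would otherwise pay for their test, is met by facility reimbursement alone.

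**Step 2. Route to the primary outcome**

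A SOC man is told self-testing is reimbursed, buys a kit online and uploads a photo of the used kit, which the protocol accepts as verification. He then counts as tested in SOC. The effect on the difference is downwards.

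**Step 3. Reproduce the planned power**

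Inputs from the Sample size section: 42 per arm, two-sided alpha 0.05, Fisher's exact test, SOC 10%, difference about 32 points (so HCVST 42%), stated power 90%.

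Power = Σᵢ Σⱼ Bin(i; 42, p₁) × Bin(j; 42, p₂) × 1{two-sided Fisher p ≤ 0.05}, with i and j from 0 to 42.

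With p₁ = 0.42 and p₂ = 0.10, power = 0.910. The stated 90% is reproduced, with no deduction for loss to follow-up.

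**Step 4. Let the SOC rate rise**

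The documents give no figure for the rise, so the SOC rates above the planning value are assumptions.

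| HCVST | SOC | Difference (points) | Power, 42 per arm |
|---|---|---|---|
| 42% (planning) | 10% | 32 | 91% |
| 42% | 15% | 27 | 74% |
| 42% | 20% | 22 | 51% |
| 40% (trial 2 pilot) | 10% | 30 | 87% |
| 40% | 15% | 25 | 67% |
| 40% | 20% | 20 | 44% |
| 78.9% (trial 1 pilot) | 20% | 58.9 | about 100% |
| 78.9% | 40% | 38.9 | 95% |

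In head counts, a rise from 10% to 15% is 0.05 × 42 = 2.1 extra SOC testers, and a rise to 20% is 0.10 × 42 = 4.2.

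With the protocol's 20% loss (0.8 × 42 = 33.6, taken as 34 per arm), the three 42% rows become 82%, 61% and 41%.

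**The case against.** The strongest reply is that the two sections need not conflict. A reader might infer that the Discussion excludes self-testing, but it never says so. What it names is a subset of what Data collection names, and Data collection is the operative text. That stands: this is a difference in scope between two accounts of one notice, not a flat contradiction. It still leaves sites without a single message.

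A reader might also infer that SOC men are offered the intervention free. The documents do not support that. A SOC man must find a kit, pay first and then claim, and he gets no study delivery, study instructions or study video. The contrast in provision survives; what goes is the price. It is not even certain that his claim would be paid, because the proof includes a test report, a term the same section uses for facility tests, while self-tests are verified by a photo of the used kit. Nor does the silence of Table S1 help the concern, since the table omits facility reimbursement too.

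Further points stand in part. The bias is towards zero, so it cannot manufacture a benefit. Kits are on open sale, so some SOC self-testing can happen whatever the notice says. The follow-up survey already records testing method, and the economic plan already separates the cost per person self-tested from the cost per person tested in a facility.

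Finally, equal reimbursement with unequal delivery is a defensible pragmatic design. But the protocol does not claim that design, and the rationale in the Discussion concerns facility tests.

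**Conclusion.** The concern holds as a mismatch in scope that should be resolved, with a likely bias towards zero if the wider notice is used. The direction follows from the outcome definition. The size cannot be derived from the documents: it depends on how many SOC men would buy and claim for a kit because of the notice.

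The power figures are illustrative. They combine assumed SOC rates with an HCVST rate of 42%, which comes from the protocol's detectable difference and is not its expected effect. It would be wrong to read them as showing that both trials lose their power. At trial 1's pilot rate, power stays at about 95% or more up to a SOC rate of 40%. In trial 2 the pilot SOC rate was 0 of 5, so a rise need not start from 10%. The power concern therefore falls on trial 2, or on an effect smaller than the pilot's, which the protocol itself allows for when it warns that the pilot effects may be exaggerated.

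The effect on the estimated difference and on the cost comparison does not depend on power. That makes this worth correcting, but not a flaw that invalidates the design.

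**What to change.** Bring the reimbursement sentence under Data collection into line with the Discussion, so that the enrolment notice to all participants covers facility-based HCV testing and no longer offers reimbursement of self-testing. Use the same wording in the enrolment information at all seven sites.

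Keep the primary analysis by randomised arm, with any verified SOC self-test still counted as a test. Report the number of SOC self-tests in each trial as crossover, using the method item already in the follow-up survey.

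The cost is a wording change and one descriptive line in the results. The downside is that a SOC man who buys a kit himself is not repaid, which leaves a small price difference for that route.
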